### Primary outcome measures

ADL with Lower extremity functional scale (LEFS).

Outcome variables gauging functional outcome:

Score on LEFS [20] at 0, 2, 6, 12 and 26 weeks post-surgery.

LEFS: This is a questionnaire containing 20 questions about a person’s ability to perform everyday tasks. The LEFS can be used by clinicians as a measure of patients’ initial function, ongoing progress and outcome, as well as to set functional goals. The LEFS can be used to evaluate the functional impairment of a patient with a disorder of one or both lower extremities. It can be used to monitor the patient over time and to evaluate the effectiveness of an intervention. The questionnaire’s rating scale consists of 80 points. The lower the score the greater the disability [20].

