We have developed an early permissive weight bearing post-surgery rehabilitation protocol, where progression of weight bearing is guided by the subjective experience (e.g. pain, weight bearing tolerance) of the patient and therapist, and objective parameters (e.g. temperature of the limb, edema, and gait parameters) are registered. This early permissive weight bearing protocol has previously been implemented and validated in our rehabilitation center since 2005. Follow up and evaluation of the permissive weight bearing protocol are ensured by recording and documenting weight bearing milestones (e.g. walking with 2 crutches, walking with 2 canes, walking with one cane and walking without any walking aids) in a database. Retrospective analysis of the complications that occurred while using this new protocol showed a complication rate of 10%, non-unions and infections being the most common complications. A comparison of our complication rate to data reported in literature that were based on protocols using the existing guidelines, such as the current non-weight bearing guidelines (AO protocol), showed lower complication rates for all our groups treated according to the permissive weight bearing protocol. Recent literature has reported composite postoperative complication rates of up to 37%, with an average of 10–20% in patients with lower extremity fractures [7–16].

In our study we want to compare our early permissive weight bearing protocol to the currently existing AO treatment guidelines in a prospective comparative cohort study. In addition to the follow up, featuring clinical documentation and registration of weight bearing milestones, new techniques for ambulatory measurements of loading (i.e. gait analysis by means of insoles) and non-invasive quantification of muscle mass will be used. This study will be performed in patients with (peri)- or intra-articular fractures of the pelvis/acetabulum and lower extremity after surgical treatment for which existing guidelines do not allow early full weight bearing in the first 6–12 weeks.

The primary research question is: How do the current guidelines (AO guidelines) and a permissive weight bearing protocol compare as to early recovery of functional outcome in trauma patients with fractures of the lower extremities after 6 months?

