### Hypothesis

#### Hypothesis 1

The permissive weight bearing protocol will lead to 1A: a better outcome at activity level (as measured with the Lower Extremity Functional Scale (LEFS)), 1B: a better early recovery at function level (as measured with the Brunnstrom Fugl-Meyer (BFM) test), 1C: a better participation (as measured with the SF-36) and 1D: a better quality of life (as measured with the EQ-5D-5L) in the first 6 months post-surgery, as compared to patients who are treated according to current standard guidelines. It is expected that in the long-term (i.e. 1 year) functional outcome will be similar between the treatment groups and will therefore not be the primary focus of this study [3]. We have chosen for the three scales mentioned above to cover the major outcome levels in the ICF model [17].

#### Hypothesis 2

The permissive weight bearing protocol for trauma patients with fractures of the lower extremities is more cost-effective compared to the non-weight bearing protocol and current guidelines.

#### Hypothesis 3

The rate of complications (e.g. failure of osteosynthesis, secondary displacement of fracture parts, non-union, infections) is equal or lower in patients who are treated according to the permissive weight bearing protocol compared to patients treated according to standard current guidelines.

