### Sample size calculation

To date, no exact data on differences in functional outcome (LEFS) between the two different aftercare treatments for patients with fractures of the lower extremities are available. In two studies, the LEFS is expected to be 65 points (SD 10) in the non-weight bearing group [18, 19]. In this study we consider an increase in LEFS of 10% or more in the permissive weight bearing treatment group. In order to detect a difference between two independent means (two groups), assuming that an equal number of patients in both groups will be included, with an alpha of 5% and beta of 20% (power 80%), the sample size should be at least 51 for both groups, thus leading to a total number of 102. Anticipating a 20% drop out and 10% more patients to obtain equal groups, a total of 134 patients have to be recruited.

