### Data collection

Baseline measurements will be performed as soon as possible post-injury (= week 0). Further measurements will be taken at week 2, week 6, week 12 and week 26 post trauma (see also flow chart, Fig. 1).

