### Statistical analyses

Data will be recorded in the digital study database and will be analyzed by a researcher blinded to the study groups the patients entered into.

Variations in case mix between centers can influence the interpretation of outcome data. Therefore, for each of the data sets collected, differences in outcome variable between the services will be tested using multiple MANCOVA’s, entering various indicators of case mix as co-variates (i.e. age, gender, ISS, number of complications, etc).

Insole pressures will be presented as mean ± SD. Statistical analysis of pressures involves repeated-measures two way ANCOVA using time as the within-group factor and treatment protocol as the between-group factor. Post-hoc group comparison at the different time points is only performed when the overall repeated-measures tests are statistically significant. A Bonferroni approach will be used to avoid spurious false positive findings. All scores will be tested for normality using the Shapiro-Wilk test. Multilevel factor analysis will be performed to determine independent factors related to the primary outcome parameter functional outcome.

Statistical analysis will be performed using the Statistical Package for Social Sciences (SPSS, IBM), version 23. Level of significance will be set at alpha< 0.05.

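### No LEFS visit or summary is named as the deciding comparison, and the planned MANCOVAs are not the single comparison of means that was sized, so control of the primary error rate is not shown

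*Protocol article*

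**What the plan says.** All references are to the Protocol article.

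- **Outcome.** Primary outcome measures gives "Score on LEFS [20] at 0, 2, 6, 12 and 26 weeks post-surgery", which is a baseline and four follow-up visits. No visit, average or slope is singled out.
- **Target.** The primary question in Background asks how the two policies "compare as to early recovery of functional outcome in trauma patients with fractures of the lower extremities after 6 months". Hypothesis 1 expects a benefit "in the first 6 months post-surgery, as compared to patients who are treated according to current standard guidelines".
- **Time origin.** Primary outcome measures counts weeks from surgery. Data collection says "Baseline measurements will be performed as soon as possible post-injury (= week 0" and then "Further measurements will be taken at week 2, week 6, week 12 and week 26 post trauma".
- **Sample size.** Sample size calculation states that "the LEFS is expected to be 65 points (SD 10) in the non-weight bearing group" and that "we consider an increase in LEFS of 10% or more in the permissive weight bearing treatment group". It sizes one difference between two independent means, at 5% alpha and 80% power, and arrives at 51 per group. It does not say at which visit these values apply.
- **Analysis.** Statistical analyses plans several MANCOVAs for each data set with case-mix covariates. A repeated-measures ANCOVA for insole pressures follows, then a rule that visits are compared only after a significant overall repeated-measures test, then a sentence on Bonferroni. The section closes with "Level of significance will be set at alpha< 0.05".

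**The concern.** The primary question, the hypothesis, the outcome definition, the sample size and the analysis should all describe one comparison. Here they do not, and the choice affects the answer. Under Interventions, controls bear no weight for 6 to 12 weeks and then increase loading by 25% a week. Three or four such steps put full loading at roughly week 9 (6 + 3) to week 16 (12 + 4). LEFS at weeks 2 and 6 is therefore taken while controls are still restricted, and week 12 may be. Week 26 comes after the restriction has ended. Hypothesis 1 also expects the groups to be similar by one year, so any difference is expected to shrink with time.

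With no visit fixed in advance, the one that decides the study could be chosen after the results are seen. The test reported as primary would also not be the test that was sized.

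**Working it through.** **1. The plan's own sample size**

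Inputs from Sample size calculation: control mean 65, SD 10, alpha 5%, power 80%, equal groups. Reading the 10% increase as relative gives 0.10 × 65 = 6.5 points, so d = 6.5/10 = 0.65. Whether the test is one- or two-sided is not stated.

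Formula: n per group = 2(z_alpha + z_beta)² / d².

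- Two-sided: 2(1.960 + 0.842)² / 0.65² = 37.2, so 38 (39 by the exact t-test).
- One-sided: 30.

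The stated 51 is not reproduced at 80% power. It does appear with two-sided alpha and 90% power (50 normal, 51 t-test). Power at 51 per group, two-sided: 0.65 × √(51/2) − 1.960 = 1.32, which gives 90.7% (90.2% by the t-test). The departure is on the safe side for one comparison.

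**2. Reading A: each follow-up visit tested separately at 0.05, any one counting**

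- Independent tests: 1 − 0.95⁴ = 0.185.
- Correlated visits: simulation of four equally correlated two-sided z-tests, 1,000,000 draws for each correlation. The correlations are assumptions, because the document gives none.

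| Correlation between visits | Family-wise error |
|---|---|
| 0 | 18.5% |
| 0.3 | 17.4% |
| 0.5 | 15.6% |
| 0.7 | 13.1% |
| 0.9 | 9.4% |

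**3. Reading B: the same four tests with Bonferroni**

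Per-visit alpha is 0.05/4 = 0.0125. The requirement at d = 0.65 is 2(2.498 + 0.842)² / 0.65² = 52.8, so 53 per group (55 by the t-test). With 51 per group, power per visit is 78% (normal) or 77% (t-test). Error is controlled and power falls just short of 80%.

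**4. Reading C: one MANCOVA taking the four visits jointly**

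The overall test holds 5%. It asks whether the vectors of adjusted means differ in any way. It has no direction, can reject when each policy is ahead at a different visit, and gives no difference in LEFS points. Hypothesis 1A claims a better outcome, and the sample size concerns a difference of 6.5 points. The joint test addresses neither directly.

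**5. Which reading applies**

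Statistical analyses gives neither the number of MANCOVAs nor their dependent variables, so the text does not decide between A, B and C. Only under B is there both error control and a directional comparison in points, and the document does not say that B applies to LEFS.

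**The case against.** Several counter-arguments deserve weight.

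- **Multiplicity is addressed.** The Bonferroni sentence carries no restriction, and the next sentence, on normality of all scores, is plainly general. A reader might infer from the placement that Bonferroni applies to the insoles alone, or that the primary error rate is uncontrolled. Neither is established: the scope is ambiguous, and a joint MANCOVA would hold 5% by itself. What stands is that the text does not show control for LEFS.
- **Nobody says visits will be tested one by one at 0.05.** This is correct. The figures of 9% to 18.5% belong to Reading A only and are not the plan's error rate.
- **The two wordings of the target may describe the same six-month window, and measuring during the restriction suits a study of early recovery.** This is fair as to intent. A window containing four visits still needs a rule for which visit or summary decides, and none is given.
- **A multilevel factor analysis of functional outcome is also planned.** Its stated aim is to find factors related to the outcome. It does not define the treatment contrast.
- **The analysis plan may settle this.** It may add detail, but the question, hypothesis, outcome and sample size are all stated in this article and do not match one another.

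A reader might also infer that patients with a missing visit will be dropped, because MANCOVA commonly needs complete outcome vectors. The article does not say so. It gives only a 20% loss allowance, and handling of missing data is commonly left to the analysis plan. That inference forms no part of this point.

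**Conclusion.** The point holds in a limited form. LEFS is primary at four post-baseline visits with no deciding visit or summary, its target and time origin are worded inconsistently, and the test that was sized is not the test that is planned. Control of the primary error rate is therefore not shown, which is weaker than saying it is absent.

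The size depends on the reading:

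- separate unadjusted tests: 18.5% if independent, and 15.6% down to 9.4% at assumed correlations of 0.5 to 0.9;
- a joint MANCOVA: 5%, but no directional answer in LEFS points;
- Bonferroni over four visits: controlled, with 77% to 78% power per visit at 51 per group.

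These power figures assume a two-sided test, a 6.5-point difference and SD 10 at the visit concerned, and independent patients. The matter should be settled before analysis, because afterwards the deciding visit could be picked from the results.

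**What to change.** Before any outcome data are analysed:

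1. Name one primary LEFS contrast and one time origin. Week 26 fits the six-month wording of the primary question. If early recovery is the real target, the sponsor may justify an earlier visit or an average over visits, provided it is fixed in advance. Align the research question, Hypothesis 1, Data collection and Sample size calculation with that choice.
2. Replace the MANCOVA for LEFS by a linear mixed model on all visits, with protocol, visit, protocol-by-visit interaction, week-0 LEFS and baseline case-mix covariates. Report the primary contrast in LEFS points with its confidence interval.
3. Do not enter hospital as a fixed effect. Under Population, two hospitals supply only the intervention group and four only controls, so fixed hospital terms are aliased with protocol and the contrast could not be estimated. If clustering is modelled, use a random hospital intercept with a small-sample correction for six hospitals.
4. Treat the remaining visits as secondary and state that Bonferroni covers them.

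**Cost.** This changes wording and analysis specification only, with no new data. On the plan's own sizing basis no extra patients are needed, since 51 per group gives about 90% power for one visit. That figure does not allow for variation between hospitals. If such variation is modelled, power will be lower by an amount the document gives no basis to compute. The price of the change is that a difference seen only at a non-primary visit counts as secondary.

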### Secondary outcome measures

Function (Brunnstorm Fugl-Meyer)Participation (SF-36)Improvement in quality of life (EQ-5D-5L)Reduction in health and society costs (RUM)Total complication rate

Outcome variables gauging functional outcome:Score on Brunnstrom Fugl-Meyer [21] at 0, 2, 6, 12 and 26 weeks post-surgeryScore on SF-36 [22] at 0, 2, 6, 12 and 26 weeks post-surgeryScore on EQ-5D-5L [23] at 0, 2, 6, 12 and 26 weeks post-surgery

Outcome variables gauging complication rate:Failure of the osteosynthesis, defined as loosening or breakage of implantsMigration of fracture parts, defined as > 3 mm articular step-off and/or varus/valgus malalignment > 5 degreesInfection, defined as (but not limited to) purulent wound drainage, inflammation, erythema, fever, increased white blood cell (WBC) count, increased C-reactive protein (CRP) and/or increased erythrocyte sedimentation rate (ESR), necessitating admission for intravenous antimicrobial treatment and/or revision surgeryNon-union, defined as no radiographic union achieved after 6 months or no progress in healing

Outcome variables gauging compliance [5, 6, 24–26]:Self-reported adherence to the fracture-related weight bearing protocol, will be recorded in medical records by physical therapists.Peak load (% body weight) and step duration (in seconds) as measured by the Sensistep [27] insole pressure measurement system. The Sensistep will be used by the patient only during daytime. The measurements with the Sensistep will continue until the patient has shown 100% weight bearing. The time for the latter to occur, may differ between patients.

Brunnstrom Fugl-Meyer: This is a test that evaluates the degree of synergy formation. The test consists of 55 test items that can be scored on an ordinal 3 - point scale (0–2 points). The total test consists of an examination of the upper extremity, an examination of the lower extremity and an examination of the balance. For our study we will only use the examination of the lower extremity. The maximum total score concerning the lower extremities is 34 points [21].

SF-36: This is a multi-purpose, short-form health survey with 36 questions. It yields an 8-scale profile of functional health and well-being scores, as well as psychometrics-based physical and mental health summary measures, and a preference-based health utility index. The higher the score the better the participation [22].

EuroQol: Both generic quality of life, as well as utilities, will be derived by means of the EQ-5D, which both will be administered to the patients. The EQ-5D is chosen because it is a widely used quality of life instrument (nationally and internationally) and it is recommended by the Dutch guidelines [28]. The EQ-5D contains 5 dimensions of health-related quality of life, namely mobility, self-care, daily activities, pain/discomfort and depression/anxiety. Each dimension can be rated at five levels ranging from ‘no problems’ to ‘major problems’.

Resource Use Measurement (RUM): for this study we will develop a RUM instrument especially designed for this group, based on existing questionnaires, which will measure all relevant costs aspects [29]. A resource use measure counts the frequency of defined health system resources; such as allowable charges, paid amounts, or standardized prices. Current approaches for measuring resource use range from broadly focused measures, such as per capita measures, which address total healthcare spending per person, to those with a more narrow focus, such as measures dealing with healthcare spending for an individual procedure.

Complication score:

Measurements will be taken at 6, 12, and 26 weeks post-surgery.

During scheduled visits to the physician, signs of osteosynthesis failure / infection / non-union / delayed union will be recorded in the study database.

Radiographic evaluation by a radiologist blinded for treatment allocation will be done at the same time intervals as the scheduled visits to the physician. Radiographs will be scored for signs of osteosynthesis failure / infection / non-union and migration of fracture parts, and results will be recorded in the study database.

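### Migration of fracture parts is defined by absolute position rather than change from the postoperative film, so read literally it can count an unchanged malreduction as an aftercare complication

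*Protocol article*

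**What the plan says.** All references are to the protocol article.

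- **Hypothesis 3** names the events of interest as "failure of osteosynthesis, secondary displacement of fracture parts, non-union, infections" and predicts that their rate "is equal or lower in patients who are treated according to the permissive weight bearing protocol".
- **Secondary outcome measures** lists "Total complication rate" as an outcome with four components. One of them, migration of fracture parts, is "defined as > 3 mm articular step-off and/or varus/valgus malalignment > 5" degrees. The definition does not say new, increased or changed, and it mentions no earlier film.
- **Complication score**, within the same section, sets the timing: "Measurements will be taken at 6, 12, and 26 weeks post-surgery". It adds: "Radiographic evaluation by a radiologist blinded for treatment allocation will be done at the same time intervals as the scheduled visits to the physician". Of the films it says: "Radiographs will be scored for signs of osteosynthesis failure / infection / non-union and migration of fracture parts". What physicians record at visits does not include migration, so the radiologist's scoring is its only stated source.
- **Population** and **Randomization process**: two hospitals supply the permissive weight bearing group and four others the control group, without randomisation.
- **Demographic and medical variables** separates complications before rehabilitation from those during it, and records fracture type, operation type and ISS. **Statistical analyses** names age, gender, ISS and number of complications as case-mix covariates, with an open-ended etc.

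**The concern.** The construct in Hypothesis 3, "secondary displacement of fracture parts", is movement after fixation. The operational rule describes where the fragments lie. The two differ whenever the fragments were not in perfect position when surgery ended.

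Quality of reduction is settled before aftercare begins, so aftercare cannot cause or prevent it. In this study the aftercare protocol and the hospital are the same factor. If the two intervention hospitals and the four control hospitals differ in reduction quality, an endpoint that picks up residual malreduction carries that difference into the comparison of aftercare. Blinding the radiologist does not prevent this, because the malposition is really on the film.

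If reduction quality is the same on both sides, the result is dilution. A common background of cases unrelated to aftercare pulls the ratio towards one, and Hypothesis 3 is satisfied by an equal rate.

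Among the radiographic outcomes, this one lies closest to the fear of secondary dislocation that the Background gives as a reason for cautious loading.

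**Working it through.** The plan states no figure for this endpoint, so there is none to reproduce. The check is first a reading of the rule against cases, then an illustration of size.

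**1. The literal rule applied to cases**

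| Position after surgery | Position at week 6 or later | Moved? | Counted by the written rule? | Counted by change from postoperative film, same limits? |
|---|---|---|---|---|
| 4 mm step-off | 4 mm | no | yes (4 > 3) | no (change 0) |
| 4 degrees valgus | 4 degrees varus | yes, 8 degrees | no (4 is not > 5) | yes (8 > 5) |
| 0 mm | 4 mm | yes, 4 mm | yes | yes |

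The written rule and the intended event disagree in the first two rows, in opposite directions.

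**2. Size for migration alone**

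Assumptions, none of them in the document: true migration 3% in each group; a share m already beyond the limits after surgery, from 0% to 20%; the two independent.

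Counted rate = 1 − (1 − 0.03)(1 − m)

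- m = 0: 3.0%
- m = 5%: 1 − 0.97 × 0.95 = 7.85%
- m = 10%: 1 − 0.97 × 0.90 = 12.7%
- m = 20%: 1 − 0.97 × 0.80 = 22.4%

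If m were 5% in one group's hospitals and 15% in the other's, with no aftercare effect, the difference would be 0.97 × (0.15 − 0.05) = 9.7 percentage points.

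**3. Size for total complications**

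The Background gives 10% under the permissive protocol (retrospective) and an average of 10–20% in the literature. Take 20% in control and 10% in the intervention group as true rates, a ratio of 0.10/0.20 = 0.50, with m assumed as above. Counted rate = 1 − (1 − true rate)(1 − m).

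Equal m in both groups:

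| m | Control | Permissive | Ratio |
|---|---|---|---|
| 0 | 20.0% | 10.0% | 0.50 |
| 5% | 24.0% | 14.5% | 0.60 |
| 10% | 28.0% | 19.0% | 0.68 |
| 20% | 36.0% | 28.0% | 0.78 |

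Unequal m:

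- No true difference (10% in both), m = 5% control and 15% permissive: 14.5% against 23.5%, ratio 1.62. With the shares reversed, 23.5% against 14.5%, ratio 0.62.
- True 20% against 10%, m = 10% control and 20% permissive: 28.0% against 28.0%. The true difference disappears.

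Under the change-based definition m drops out of the formula and the counted rates equal the true ones.

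**The case against.** The strongest reply is that migration and secondary displacement both mean movement, so a sensible radiologist would take 3 mm and 5 degrees as the distance moved and compare with the postoperative film. That may well happen. The label implies change, but the written criterion does not require it, so readers could apply it differently.

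A reader might also infer that the films are read singly, with no earlier film to hand, and that malreductions will certainly be counted. The article does not say so. It gives only the assessment times, and reading instructions are detail that an article commonly leaves to the full protocol. What can be criticised is the definition itself, which the article states in full with numeric limits.

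There are partial safeguards. Complications before rehabilitation are recorded separately, fracture and operation type are collected, and case mix is to be adjusted for. None of these is tied to migration, and reduction quality is not named among the covariates.

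Finally, migration is one of four components of a secondary outcome. The primary outcome is the LEFS, and complications play no part in the sample size. Confounding by hospital affects every outcome here and is not created by this definition. All of that stands and limits the weight of the point. It does not remove the mismatch between rule and hypothesis.

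**Conclusion.** The point holds as a defect in the stated definition. Followed literally, the rule can count an unchanged malreduction as a complication of aftercare and can miss a real change that stays within the limits. With treatment assigned by hospital, the possible consequences are a spurious difference in either direction if reduction quality differs, or dilution towards equality if it does not.

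The size is unknown. The range of 3% to 22.4% rests on an assumed 3% true migration, an assumed 0% to 20% malreduction, and independence of the two. At 0% malreduction this source of error vanishes.

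Two stronger readings are tempting and not supported. One is that the endpoint would measure mainly reduction quality: that follows only from particular assumed rates, and the document gives neither rate. The other is that the rule is faulty because it misses small slips at or below 3 mm or 5 degrees: any threshold does that, including the same limits applied to change.

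The definition should be corrected, but the primary analysis does not depend on it.

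**What to change.** In Secondary outcome measures, define migration as a change from the first postoperative radiograph, keeping the article's own limits: an increase in articular step-off of more than 3 mm and/or a change in varus/valgus alignment of more than 5 degrees. In Complication score, state that the same blinded radiologist scores the first postoperative film as the reference, together with the films at weeks 6, 12 and 26. Report malposition already beyond the limits on that first film separately, as a case-mix variable and not as a complication, and name it among the covariates in Statistical analyses.

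The cost is one extra film reading per patient, assuming that a routine postoperative film exists. A patient without one would have no reference, so the plan should say how such a case is classified. No extra patients or procedures are needed, and the sample size does not change.

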### Interventions

#### Permissive weight bearing

Instead of prescribing a rigorous regime of non-weight bearing, patients are instructed and trained to start weight bearing as tolerated. The limitation in weight bearing is only dependent on the patient’s perception of pain, feeling of instability, or redness and swelling at the site of the fracture. In therapy sessions the physiotherapists stimulate early weight bearing and instruct patients to perform exercises to achieve more weight bearing when tolerated. The goal of the protocol is not to achieve full weight bearing as quickly as possible, but rather to stimulate the patient to increase weight bearing depending on his ability to do so, while maintaining a safety margin to avoid complications or to detect complications early.

Non-weight bearing or restricted weight bearing (current guidelines or AO-guideline):

The standard aftercare treatment in surgically treated trauma patients with (peri)- or intra-articular fractures of the lower extremities is non-weight bearing or partial weight bearing [3]. According to the AO-protocol, postoperative management of (peri)- or intra-articular fractures of the lower extremities consists of non-weight bearing for 6–12 weeks followed by partial weight bearing with a 25% increase in weight loading every week [1]. Non-weight bearing is taught as per the institutional standard, based on the prescribed aftercare treatment. Insole pressure measurement system will be used to monitor the weight bearing and the compliance of the patients (see below).

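### Insole measurement ends when load reaches 100%, but the planned comparison over time needs values after that point, so the later group contrast in this compliance outcome is likely to be understated

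*Protocol article*

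**What the plan says.** Under Secondary outcome measures, the protocol article lists the insole compliance variables as "Peak load (% body weight) and step duration (in seconds) as measured by the Sensistep [27] insole pressure measurement system". It then sets the end of measurement: "The measurements with the Sensistep will continue until the patient has shown 100% weight bearing". It adds: "The time for the latter to occur, may differ between patients".

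Under Statistical analyses, the insole data are to be reported as mean ± SD, and "Statistical analysis of pressures involves repeated-measures two way ANCOVA using time as the within-group factor and treatment protocol as the between-group factor". Tests at single time points depend on the overall result: "Post-hoc group comparison at the different time points is only performed when the overall repeated-measures tests are statistically significant". The article gives no rule for values after a patient's measurement has ended.

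The Interventions section describes two different loading courses. In the permissive group, "patients are instructed and trained to start weight bearing as tolerated". The AO guideline prescribes "non-weight bearing for 6–12 weeks followed by partial weight bearing with a 25% increase in weight loading every week".

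Demographic and medical variables includes the date on which the insoles show full weight bearing. The article describes no analysis of that date.

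**The concern.** The measured quantity itself decides when measurement ends. Once a patient has stopped, the later value is missing because the load was high. A comparison of group means over time then rests, at each later point, on patients who are still loading below 100%.

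If both groups stopped at the same pace, this would pull both means down about equally. The two protocols are meant to differ in exactly this respect, so the permissive group should lose its high-loading patients sooner. Classical repeated-measures ANCOVA also needs a value for each patient at each time point. If incomplete patients are deleted, those who progressed fastest disappear from the early time points as well.

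The article reports poor compliance with restricted weight bearing and uses the insoles to monitor it. In a non-randomised study these data help to show whether the two protocols differed in practice. The planned comparison tends to hide that difference.

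**Working it through.** **No stated figure to reproduce.** The article gives no expected insole values and no sample size for this comparison. Steps 2 and 3 are illustrations under assumed courses.

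**1. Stopping times implied by the text.** A compliant control bears no weight for 6 to 12 weeks and then gains 25% a week. Full load comes 3 weeks later if the first 25% is allowed at once, and 4 weeks later otherwise: 6 + 3 = 9 weeks at the earliest, 12 + 4 = 16 weeks at the latest. Permissive patients load from the start as tolerated, so earlier stopping is expected. No figure is given for them.

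**2. Share still measured, assuming normally distributed times to 100%.** The share still measured at week w is 1 − Φ((w − mean)/SD). Load is assumed to rise linearly to 100% at the patient's own time.

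| Group (assumed mean, SD in weeks) | Week 6 | Week 12 | Week 26 |
|---|---|---|---|
| Permissive (8, 3) | 1 − Φ(−0.67) = 75% | 1 − Φ(1.33) = 9% | about 0% |
| Control (13, 2.5) | 1 − Φ(−2.8) = 99.7% | 1 − Φ(−0.4) = 66% | about 0% |

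At week 6 the permissive patients still measured average 68% of body weight, against 76% for the whole group; the control mean hardly changes. The contrast is therefore about 8 points too small.

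With SD 3 and the permissive mean moved from 6 to 12 weeks, the share still measured at week 12 runs from 1 − Φ(2) = 2% to 1 − Φ(0) = 50%.

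**3. Milder courses.** Simulation with 51 patients per group, 1,000 runs, time points at weeks 2, 6, 12 and 26, and measurement ended after the first value of 100% or more. Entries are the permissive minus control difference in peak load (% body weight). "Full" means as if measurement had continued; "available" uses whatever was measured; "complete" uses only patients with all four values.

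- A: permissive means 45/70/90/100, control 15/30/70/98, between-patient SD 15, within-patient SD 10.
- B: permissive 50/80/95/100, control 20/40/75/98, same SDs.
- C: means as in A, SDs 10 and 8.
- D: permissive 35/60/80/95, control 15/30/65/92, SDs 15 and 10.

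| Course | Complete series, permissive / control | Week 2: full → complete | Week 12: full → available → complete | Week 26: full → available |
|---|---|---|---|---|
| A | 71% / 95% | 30.0 → 25.2 | 19.9 → 18.6 → 13.0 | 2.0 → −2.9 |
| B | 59% / 92% | 30.2 → 23.9 | 20.0 → 16.9 → 11.4 | 2.1 → −4.1 |
| C | 78% / 99% | 30.1 → 27.3 | 20.0 → 19.8 → 15.6 | 2.0 → −0.7 |
| D | 86% / 97% | 20.0 → 17.6 | 15.1 → 14.6 → 11.6 | 3.2 → 0.7 |

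With available data, weeks 2 and 6 are essentially unchanged, and the loss falls on weeks 12 and 26. With complete cases, the early contrast shrinks too. When both groups follow the same course (permissive course D), the bias is about 0 at every time point.

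**4. Holding peak load at 100% after the stop.** At week 12 the differences become 19.2, 18.0, 19.9 and 14.9 for A to D, closer to full data than the available-data values. At week 26 they are −1.2, −1.1, −0.1 and 1.6, against 2.0, 2.1, 2.0 and 3.2 with full data. The repair is partial, because loads above 100% are lost.

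**Limit of both illustrations.** Controls are given some load from the start, whereas the guideline prescribes none for 6 to 12 weeks.

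**The case against.** The strongest reply is that the size is unknown and that the text leaves room for a sound analysis. Much of this stands.

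- **Time points.** Weeks 0, 2, 6, 12 and 26 are attached by name to the questionnaires and the Fugl-Meyer test, not to the insoles. The time factor could cover only early weeks, when nearly everyone is measured. The point therefore concerns later time points, not visits.
- **A large loss of permissive patients.** A reader might infer that including week 12 removes over 90% of the permissive group. That follows from one assumed scenario (9% remaining). The same scenario leaves about nobody measured in either group at week 26, so it cannot also give a week-26 comparison of slow permissive patients with most controls. In the milder courses, 14% to 41% of permissive patients are incomplete (100% − 86% and 100% − 59%).
- **Similar courses.** The Background notes that patients on restricted regimes often exceed their limits, which would bring stopping times closer. With assumed means of 10 weeks (SD 3) and 12 weeks, 25% and 50% remain at week 12.
- **Deletion.** It is usual for the classical method, but the article names the method and SPSS 23, not the procedure.
- **Unseen analysis plan.** Scoring of values after the stop is commonly left to such a plan, and its absence here is no fault.

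What does not fall is the conflict between two rules that the article does state: measurement ends on the outcome, and group means of that outcome are compared over time.

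**Conclusion.** The point holds as a mismatch between the stopping rule and the analysis of the insole data. Followed as written, with time points that run past the first stops, the two rules produce missing values that depend on the outcome and probably differ by group. Where the courses differ, the permissive minus control contrast tends to shrink. In the milder courses the week-12 loss was 0.2 to 3.1 points with available data and 3.5 to 8.6 points with complete cases, and the week-26 sign reversed in three of four.

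These sizes rest on assumed loading courses and on time points borrowed from the visit schedule. The conclusion also takes insole pressures to mean peak load, which is the natural reading. The direction is well supported; the size is not known and could be about nil.

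A reader might infer that the LEFS result becomes unreliable. The documents do not support that: the primary test does not use the insole data. Evidence that the groups differed in practice also does not rest on this test alone, since time from accident to weight bearing, the date of full weight bearing and self-reported adherence are all recorded. The change is worth making, but it concerns a compliance outcome.

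**What to change.** 1. Make time from surgery to 100% weight bearing the main between-group insole analysis: Kaplan-Meier curves and Cox regression with the case-mix covariates, censored at week 26 or at loss to follow-up. Stopping at 100% is then the event, not a source of missing data.
2. Restrict the repeated-measures comparison of peak load and step duration to an early common window in which nearly all patients in both groups are still measured. Fix the window and its time points in advance.
3. Add a sensitivity analysis that holds peak load at 100% after the stop. It should not be the main analysis: values fixed at a ceiling have no variance and fit a normal-errors model poorly, and step 4 of the working shows only partial recovery.

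**Cost.** This is a change of wording in the analysis section. The date of full weight bearing is already collected. The date of surgery is not in the listed variables, but the outcome times are counted from surgery, so it should be at hand. The downside is that loading after the stop, and loads above 100%, remain undescribed.
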